#### Qualitative data

Interview and focus group transcripts will be analysed using MAXQDA. A coding framework developed from the topic guides and WISH2 framework will be used to systematically and deductively code and analyse data. The framework will allow flexibility to capture issues from the data and from the project over time and provide a basis for mapping the evidence from qualitative data analysis against research questions.

To interrogate and interpret the qualitative data from focus groups and interviews we will use thematic analysis. Data from local residents and stakeholders will be analysed separately, so we can explore similarities and differences between the two groups. Thematic analysis categorises data and then examines the relationships and meanings in the categories to identify themes [64,65]. We will conduct a cross-sectional analysis of focus groups and interview transcripts to examine the data across each data set, and the thematic analysis to generate and explore themes or patterns of meaning within these two data sets. This will: (i) enable understanding of what transcripts contain; and (ii) identify recurring themes. We will identify recurring themes that reflect specific patterns or meaning found in the data and categorise these by applying codes to portions of data. These codes will describe a range of factors, attitudes, behaviours, allowing us to explore in more detail if and how HS2 affected people’s health and wellbeing and what factors and strategies could facilitate the process of adapting to change [66].

To select the stories for the Most Significant Change analysis, the researchers will read all the stories elicited from interviews, organise them by theme and select 10 that represent different themes and include impacts at the planning, construction, and operation stages, if available. For each of these stories, an anonymous summary will be written that is no longer than a page in length. A workshop will be held with Public Advisory Group members, with facilitation from the research team, to discuss the stories and between them select the three that they feel represent the most significant changes to mental health and wellbeing and/or the process of adapting to change.

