#### Qualitative data

While qualitative research does not define “outcomes” in the same way as quantitative research, the topics included in the guides for the interviews and focus groups are informed by the logic model framework (see Design section), the outcomes used in the cohort and administrative data research, and findings from the survey. In addition to standard focus group and interview approaches we will use an adapted version of the Most Significant Change technique [43,44] to collect stories of change to answer RQ2. This technique is well suited to interventions where anticipating all changes in advance is difficult. The method involves defining domains of change (e.g. quality of life, mental health, wellbeing), collecting significant stories of change and selecting the most significant of these.

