#### Qualitative data

For local residents we will conduct eight focus groups per data collection wave, two from each part of the Phase 2 route (Phase 2a Phase 2b West, Phase 2b East, and the section of Phase 2b East that is not proceeding as originally planned), offering one virtual and one in-person focus group to participants from each route section. Each focus group will include a maximum of 10 participants. We will also conduct 3–4 interviews for each route segment. We will conduct up to 53 interviews per data collection wave with clinical staff from participating exposed GP practices and community stakeholder representatives. These sample sizes have been determined in collaboration with the funder and should be sufficient to reach thematic saturation.

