#### Qualitative data

Participants selected from the study cohort will be invited to participate in a focus group or interview via telephone, email, or post (for survey participants, based on indicated communication preferences in their survey consent form). Other potential participants (clinical staff and community stakeholders) will be invited by email or telephone. Participants will receive an information sheet and consent form in advance and a list of dates and local venues (for focus groups) or tailored arrangements (for interviews). Each focus group will take up to 120 minutes and interviews up to 60 minutes. In addition to standard focus group and interview approaches, we will use an adapted version of the Most Significant Change technique [43,44]. Focus groups and interviews will be used to collect stories of change. Stories may be recorded with participants’ consent and transcribed verbatim. Recordings will be deleted once transcripts have been finalised. a combination of direct (interviewee’s experience) and indirect (interviewee relating stories of others’ experiences).

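### Most Significant Change stories are to be collected in focus groups and interviews, but the selection rule reads only those from interviews, so resident focus-group stories could not be shortlisted.

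*Protocol article*

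**What the plan says.** Four parts of the protocol article bear on this.

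- Outcomes: Qualitative data introduces an adapted Most Significant Change technique, alongside standard focus group and interview approaches, "to collect stories of change to answer RQ2".
- Data collection: Qualitative data names two sources: "Focus groups and interviews will be used to collect stories of change".
- Sample size: Qualitative data sets the numbers. "For local residents we will conduct eight focus groups per data collection wave, two from each part of the Phase 2 route"; "Each focus group will include a maximum of 10 participants"; "We will also conduct 3–4 interviews for each route segment". For other participants, "We will conduct up to 53 interviews per data collection wave with clinical staff from participating exposed GP practices and community stakeholder representatives".
- Analysis plans: Qualitative data gives the selection rule. For the Most Significant Change analysis, "the researchers will read all the stories elicited from interviews, organise them by theme and select 10", covering different themes and, if available, the stages of the development. A one-page summary is written for each, and a Public Advisory Group workshop then picks three.

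**The concern.** The collection step names two sources and the selection step names one. No section explains the narrowing or says that the word interviews is meant to cover focus groups.

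This is a stated rule and not a detail left to a fuller plan: the article gives the source, the shortlist size, the length of the summaries, the panel and the final number. Selection also runs in two steps. The workshop sees only the 10 summaries, so a story left unread at the first step cannot be recovered at the second.

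The restriction would fall on residents. The article describes focus groups for local residents only, while clinical staff and community stakeholders are interviewed. Focus groups are also the larger of the two resident formats by number of people. At stake is whether the showcased stories of change draw on most of the residents who take part in the qualitative work.

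**Working it through.** The plan gives no figure of its own to reproduce here, so the check is a comparison of wording followed by a count.

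**Wording.** In Analysis plans: Qualitative data, the coding of transcripts, the thematic analysis and the cross-sectional analysis each name both interviews and focus groups; for example, "To interrogate and interpret the qualitative data from focus groups and interviews we will use thematic analysis". Only the story-selection sentence omits focus groups. On its plain wording, the selection is narrower than both the collection and every other qualitative analysis.

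**Inputs, per wave (Sample size: Qualitative data).**

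- Resident focus groups: 8 (two in each of four route parts), with at most 10 people each.
- Resident interviews: 3–4 in each of four segments, so 4 × 3 = 12 to 4 × 4 = 16. The sentence stands with the resident focus groups and is read here as referring to residents.
- Clinical staff and stakeholder interviews: up to 53.

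**Share of qualitative residents outside the rule** = focus-group residents / (focus-group residents + interviewed residents).

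- 10 per group: 80/(80 + 16) = 83.3% to 80/(80 + 12) = 87.0%.
- 6 per group: 48/(48 + 16) = 75.0% to 48/(48 + 12) = 80.0%.
- 4 per group: 32/(32 + 16) = 66.7% to 32/(32 + 12) = 72.7%.

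**Share of resident stories.** The article gives no story counts, so this needs an assumption about yield. With one story per group and one per interview, it is 8/(8 + 16) = 33.3% to 8/(8 + 12) = 40.0%. With one story per interview, the focus-group share passes one half only if each group yields more than 12/8 = 1.5 to 16/8 = 2 stories.

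**Pool left for selection.** Interviewees number 12 + 53 = 65 to 16 + 53 = 69, of whom residents are 12/65 = 18% to 16/69 = 23%, if all 53 other interviews take place.

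**With the rule widened.** The resident pool rises from 12–16 people to as many as 80 + 12 = 92 to 80 + 16 = 96.

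**The case against.** The strongest reply is that this is loose wording. The selection sentence does not say that only interview stories count. In Data collection: Qualitative data, just after both formats are named as sources, the person telling a story is called an interviewee, which suggests that the authors may use interview words for both. That passage is an incomplete sentence, so it is suggestive and no more. Against it, the analysis section names both sources everywhere else. The possibility of loose wording stands, but it does not remove the mismatch.

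A second reply is that people are not stories. Ten per group is a maximum, and one member of a group may say less than someone interviewed alone. By maximum contact time, 8 groups × 2 hours = 16 hours against 12–16 hours of resident interviews, which puts the focus-group share at 16/32 = 50% to 16/28 = 57%. This stands: a reader might infer that most resident stories would be lost, but the article has no story counts to support that.

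A third is that selection is purposive. A reader might also infer that the 10 stories and the final three would come mostly from professionals' second-hand accounts. That does not follow. The researchers choose for variety of theme and stage, the 12–16 resident interviews could fill all 10 places, 53 is an upper limit, and the article plans for both direct and indirect stories.

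A fourth is that RQ2 does not rest on this technique. It supplements the standard approaches, and Table 1 assigns RQ2 to cohort, qualitative and administrative data. This stands and limits the consequence.

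Finally, the article promises a pre-registered analysis protocol for each wave and data source. It is not shown, and it may settle the matter, but it does not correct the sentence as published.

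**Conclusion.** The inconsistency is real and minor. As written, stories from the resident focus groups are collected for the technique and then cannot be shortlisted for it, without a stated reason. Its reach is best given in people: up to 80 residents per wave, the large majority of qualitative residents at any group size from four to ten. The share of stories is unknown and depends on yield per group. The shortlist could under-represent residents; nothing in the article shows that it would.

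The consequence is confined to the Most Significant Change component. Focus-group accounts remain in the coding and thematic analysis, and no quantitative result is touched. The finding rests on reading the word interviews in its ordinary sense, as the rest of the same section uses it.

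**What to change.** In Analysis plans: Qualitative data, extend the selection sentence so that the researchers read all stories elicited from interviews and from focus groups. If the restriction to interviews is intended, state the reason there and correct Data collection: Qualitative data so that it no longer names focus groups as a source of stories for this technique. Either change is a phrase or a sentence and can be carried into the pre-registered qualitative analysis protocol for each wave. Widening the rule costs some extra reading time: the stories from eight focus groups per wave.

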#### Administrative data

The main analysis will use a multivariable regression framework, which will compare exposed and unexposed practice populations and look at the difference in differences over time in the four administrative mental health outcomes. For the outcomes that are proportions or counts, we will disaggregate the practice level measures and use a person level modelling framework (with practice level covariates). Models used will depend on the characteristics of the outcome variables, but we anticipate using mixed or fixed linear, logistic and Poisson models.

We will adjust for age, gender, calendar month and index of multiple deprivation an aggregate measure of the degree to which people living in a particular area of the UK have the income, health, education, housing or other resources required to meet their needs (https://www.gov.uk/government/statistics/english-indices-of-deprivation-2019). We will additionally adjust for pre- and post-intervention trends in the outcomes to explore whether these are differential among exposed and unexposed practices. We will weight the contribution of exposed practices based on the percentage of the practice population that live within 5km of the proposed route. Where appropriate, we will assess the parallel trend assumption of the difference-in-difference approach through visual inspection of plots for each outcome. We will evaluate it analytically by conducting sensitivity analyses using the Omitted Variable Framework by Cinelli & Hazlett for regression models and extended by Landon & Zimmerman for DiD analyses [67,68].

#### Health economic analysis

*Change in costs of health and social care use*. In the cohort survey, we will collect participant-level data on health and social care service utilisation (primary and secondary care, personal social services, medications) during the previous three months and analyse this using a difference-in-difference approach. For the economic analysis we will apply unit costs to these utilisation measures from published sources [69–71], and repeat the difference-in-difference approach. This will give the participant-level change in costs of health and care service use over the previous three-month period associated with each wave of the HS2 development (including, separately, the Phase 2b sections not proceeding as planned).

We will repeat these analyses for population subgroups (e.g. based on combinations of socioeconomic status, age, gender and urban/rural status). Selection of specific groups will be informed by the cohort surveys and interview and focus group results. The participant-level change in costs for each subgroup will then be extrapolated pro rata to the actual duration of each wave of the development, and the analysis will be repeated for each wave of the development separately for Phase 2a and 2b. This will result in a dataset of changes in health and social care costs per person for each wave of the HS2 development that varies by population subgroup. We will then multiply these cost changes by the number of people in each population subgroup potentially affected by different phases of the HS2 development based on Office for National Statistics and National Health data, as defined according to our sampling strategy for the cohort surveys, to compute the total change in health and social care costs at the population level associated with the HS2 development by phase and wave. This will require data on the total number of people in each subgroup living within 5km of the route, which will be obtained from the sources used for the administrative data analysis. We will undertake extensive, deterministic sensitivity analyses around our central estimates of these potential impacts, varying the difference-in-differences, unit costs, durations and population sizes.

*Monetised impacts on quality of life*. In the survey, we will collect participant-level data on health related quality of life using EQ-5D-5L [72]. We will use the EQ-5D-5L data to compute utility scores for each participant using the Crosswalk Index Value Calculator [73]. We will repeat the difference-in-difference approach described for the survey data using EQ-5D-5L utility scores as the outcome, which will give the participant-level change in utility scores associated with each wave of the HS2 development.

As above, we will repeat this analysis for population subgroups. The participant-level change in utility scores for each subgroup will then be extrapolated pro rata to the actual duration of each wave of the development to compute the change in quality-adjusted life years (QALYs), resulting in a dataset of QALY changes per person for each wave of the HS2 development that varies by population subgroup. We will then multiply these changes by the number of people in each population subgroup potentially affected by different phases the HS2 development (as above) to compute the total QALY changes at the population level, by phase and wave. These values will be monetised by multiplying the total QALY changes by the prevailing values for a QALY, which currently range from £15,000 per QALY on the basis of the opportunity cost to the NHS to £60,000 per QALY on the basis of willingness-to-pay [74–76]. These will also be subject to extensive sensitivity analyses, varying the DiDs, durations, and population sizes as well as the QALY valuations.

#### Triangulation of results and incorporation of stakeholder feedback

The analysis integration plan for the study is informed and driven by the WISH2 framework and the Pillar Integration Process developed by Johnson, Grove and Clarke [77]. The Pillar Integration Process is a structured mixed methods analysis framework that guides the way in which quantitative and qualitative data are integrated [77]. It enables the systematic visualisation of the analysis process in a way that integrated findings can be traced back to their original sources, enhancing transparency and replicability [77]. Value beyond what is brought by the individual methods comes from the additional thinking and processing of data required to bring together and organise findings into the joint display and populate the ‘pillar building’ column, thus increasing the quality of the integration [77]. This process also encourages researchers to reflect on the limitations of each data source, for instance, the appropriateness of the research questions and comprehensiveness of the research tools.

The logic model and research questions will provide a framework for the integration of findings. We will create a joint display for each research question. Theoretically, joint displays are used to present quantitative and qualitative data from the same ‘case’, which can mean the same participant or similar themes/topics, phenomena or settings [78]. For this evaluation, data will primarily be integrated at the level of themes, with labels added to the joint displays so that data organisation is aligned with the WISH2 framework. We will not integrate data at a participant-level, but to support the exploration of health inequalities we may produce separate joint displays that bring together data across sources (survey, administrative data analyses, interviews, and focus groups) for particular groups. The findings from each wave will be used to update the WISH2 framework iteratively and inform the data collection tools and approaches for the next wave.

After wave 2 and wave 3, we will obtain feedback from local stakeholders and the WISH2 Public Advisory Group, including exploration of any gaps identified. Workshop results will be included with other study data in the final synthesis for each wave. Two workshops per wave (4 in total) will be held with local stakeholders in areas from which participants have been recruited and will act as a forum for stakeholders to provide feedback on study results prior to publication.

### Data management

The study has been pre-registered (ISRCTN58916738; https://www.isrctn.com/ISRCTN58916738). We will pre-register analysis protocols for each WP and each wave of data collection using the Open Science Framework (https://osf.io/hqgdt).

The paper forms used for consent and collection of quantitative interview data, and all personal identifying information of participants will be securely destroyed 12 months after the completion of the study, once linkage between the quantitative survey data and medical records have been completed and data have been checked to ensure that no reference to the original data collection instruments is necessary.

It is a stipulation of the funding for this project that all the data it generates are made publicly available to other researchers in de-identified form. We will share de-identified versions of the data from the surveys, interviews, and focus groups. In the case of the survey data this will consist of the survey responses, age at survey, gender, and distance from any part of the HS2 route but not name, date of birth, address or NHS number. In the case of interviews and focus groups only the anonymised transcripts of these will be shared, not the recordings to preserve privacy. We will share these data using the UK Data Service (https://ukdataservice.ac.uk/). This means only people registered and approved by the UK Data Service will access to information from this study, and we will know who has been given access and for what reason.

### Ethical considerations and declarations

This study has been reviewed and approved by the East of England (Cambridgeshire and Hertfordshire) Research Ethics Committee (22/EE/0292) and the Health Research Authority (IRAS302856). During the data collection phase of the study, participants will be free to withdraw at any time, without giving a reason. Their sensitive personal data will be destroyed and the participant will not be contacted again by the research team for any future waves of data collection. Data already collected as part of the study will be retained. We are aware that some of our participants may find issues that arise during data collection sensitive and potentially upsetting and hence we are being guided by our Public Advisory Group and our Public and Patient Involvement Lead to advise prior to approvals and amendments being sought.

Any amendments to the study protocol related to survey, qualitative interviews, or focus groups will be submitted to the Health Research Authority and Research Ethics Committee for necessary approvals. Other significant amendments will be recorded in the ISRCTN registry entry for the study (www.isrctn.com/ISRCTN58916738) and/or relevant pre-registrations and analysis plans available on OSF (https://osf.io/hqgdt).

### Dissemination

We are iteratively developing a dissemination strategy in collaboration with our Public Advisory Group. However, we anticipate that it will include:

Tools for disseminating results for each wave including: funder reports, academic papers and conference attendance, infographic summaries, plain English leaflets, message-led policy briefings, blogs and podcasts/videos.Public Advisory Group involvement may include co-authorship, co-presentation and bespoke dissemination for targeted public audiences.A public website that tracks progress and provides access to these dissemination tools (this is already in place and has been refined following Public Advisory Group input - www.wish2.org –and will expand as the research progresses).Tailored dissemination approaches for different stakeholder groups using different combinations of dissemination tools.After wave 2 and wave 3, workshops to obtain feedback from the stakeholder groups.

